# INulin-type β-fructans supplementation to modulate gut microbiota and assessment of its effects on health status and GUT-SKIN axis parameters in patients with psoriasis (INGUTSKIN): the 8-week, randomised, double-blind, placebo-controlled clinical study protocol

**DOI:** 10.1186/s12937-026-01316-8

**Published:** 2026-03-17

**Keywords:** Chronic skin inflammation, Prebiotic, Inulin-type fructans, Nutritional intervention, Quality of life, Gut microbiota, Intestinal barrier, Volatile organic compounds, Oxidative stress, Metabolic parameters

## Abstract

**Background:**

A strong, bidirectional association exists between gastrointestinal health and skin homeostasis in many chronic skin inflammations, including psoriasis (PS). It is postulated that, apart from genetic predisposition, the rise of local and systemic immune response in PS could be a consequence of intestinal dysbiosis associated with increased intestinal permeability. We hypothesised that restoring gut microbiome homeostasis and proper functioning of the intestinal barrier in PS patients would alleviate the inflammatory symptoms and severity of the skin lesions. The study aims to determine the effect of chicory-derived inulin-type β-fructans (ITFs) on health-related parameters in mild PS patients through molecular analysis of gut microbiota characteristics and assessment of a wide spectrum of biomarkers of the gut-skin axis.

**Methods:**

The randomised, placebo-controlled clinical trial (RCT) with prebiotic intervention is proposed. Adult mild PS patients (Psoriasis Area and Severity Index; PASI < 10) with a body mass index (BMI) < 30 kg/m^2^ following an omnivore diet will be enrolled into the trial and randomized to one of two groups: prebiotic (receiving 15 g/per day of ITFs) or placebo (receiving 15 g/per day of maltodextrin) for 8 weeks in a double-blind manner. Body composition, clinical parameters, nutritional status, quality of life, immune and inflammatory parameters, intestinal barrier permeability, characteristics of faecal bacteria, and metabolic dysfunction markers will be determined at baseline and after supplementation. Compliance and adverse reactions will be evaluated.

**Discussion:**

The dysregulation in intestinal microbiota-host interplay is connected with the development of many chronic skin inflammations, including PS. A proper diet is a relatively easy-modifiable factor that may influence the course of PS treatment. Among dietary components, prebiotics have garnered our interest as ingredients with a proven ability to enhance host health by modulating the gut microbiota. With the proposed RCT, we will determine the impact of ITFs on gut microbiota characteristics and evaluate whether this ITFs-induced microbiota modulation is an effective method to alleviate inflammation and reduce the severity of skin lesions in PS. We expect that the RCT results will enable the introduction of personalised dietary therapy with prebiotic ITFs, which, unlike other PS therapies, would not pose a high risk of side effects.

**Trial registration:**

ClinicalTrials.gov Registration Number: NCT05971992.

## Background

Psoriasis (PS) is a non-contagious chronic skin inflammation that occurs in approximately 2–3% of the global population in most ethnic groups [1]. It is characterised by various symptoms, including flaky skin (patches), itchiness, and redness of the affected area. In most cases (approximately 70–80%), psoriatic skin lesions are mild [2] and do not require systemic treatment or immunosuppressants, which may exert severe side effects. Nevertheless, novel and safe therapeutic approaches are still demanded to treat psoriasis lesions.

Although the pathogenesis of PS is not fully understood, it is known that the main cause of PS development is genetic predisposition [3, 4], which, in combination with environmental factors may lead to a dysregulation of the immune responses, observed as accelerated tumour necrosis factor(TN)/interleukin-23 (IL-23)/IL-17 axis, and hyperproliferation of epidermal keratinocytes.

Recently, considerable interest has focused on the interactions among the intestinal microbiota, intestinal barrier, and immune system in PS [5–7]. The studies by Sikora et al. [6] support the hypothesis that the inflammatory process in PS may disrupt the gastrointestinal barrier. In addition, recent studies indicate that the intestinal microbiome profile of PS subjects significantly differs from that of healthy subjects [8–11]. Thus, the so-called “gut-skin axis” has been considered a key factor in the aetiology of PS and a potential therapeutic target [12].

The relationship between dietary habits and the severity of psoriasis has rarely been studied. Meanwhile, epidemiological studies have shown that individuals with PS have unbalanced macronutrient intake, in particular higher intakes of simple carbohydrates and total fat, and lower intakes of protein, complex carbohydrates, dietary fibre, omega-3 polyunsaturated fatty acids (PUFAs), and vegetables [13, 14]. Diet is a relatively easy-to-modify factor that may influence the course of PS and the effectiveness of its treatment. The application of dietary fibre in the diet has been reported to show systemic and intestinal anti-inflammatory effects [15, 16]. Fibre may also promote the growth of commensal bacteria and increase the resistance to the colonisation of pathogenic bacteria, correcting the dysbiosis in gut microbiota in PS [17].

Prebiotics are dietary ingredients with great potential to influence human health beneficially through their impact on the growth and/or activity of health-promoting bacteria that colonise the gastrointestinal tract. Consumption of prebiotics resulted in a significant increase in bifidobacteria and lactobacilli and a reduction in the count of pathogenic bacteria, such as clostridia [18]. Moreover, prebiotics influence the activity of the immune system and certain immunological biomarkers, mainly due to a modulation of gut bacterial composition and activities [19–21]. Thus, prebiotics as gut microbiota-modulating agents should become a research target to alleviate inflammation and the severity of skin dermatitis.

Inulin-type fructans (ITFs) are a group of naturally occurring plant carbohydrates that are classified as prebiotics. The ITFs have many beneficial effects on inflammatory bowel diseases, including affecting the histological picture of the intestine (proliferation in the crypts and goblet cells, longer intestinal villi), changing the profile of mucins and modulating endocrine and immune functions [22]. Moreover, they have great potential as agents for improving or maintaining a balanced intestinal microbiota. Despite the benefits resulting from ITFs intake, their efficacy in managing skin inflammation is not widely documented. Thus, high-quality studies analysing the effect of prebiotics on PS subjects are urgently needed.

### Study objective

The primary aim of this original and complex randomised controlled trial (RCT) is to determine the effect of chicory-derived ITFs supplementation on health-related parameters in PS patients through molecular analysis of gut microbiota characteristics and assessment of a wide spectrum of metabolic parameters and biomarkers of the gut-skin axis. We expect that prebiotic ITFs, as a dietary supplement, will provide several health benefits to PS subjects beyond the gastrointestinal microbiota, such as neutralising systemic inflammation, reducing the severity of skin lesions, and rebuilding/stabilising the intestinal barrier, without causing side effects. Additionally, we expect the proposed RCT to determine whether the identified health-related benefits are evoked by compositional and/or functional changes of the intestinal bacterial communities.

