Statistical analyses and visualisations will be performed using the R software (www.r-project.org), Statistica 14 software (StatSoft, USA) or GraphPad Prism version 10.0.3 (275) for Windows, GraphPad Software, LLC (Boston, MA, USA). The data within groups will be tested for normality using the Shapiro–Wilk test. Levene’s test will be performed to assess the homogeneity of variances within groups. For secondary outcomes and cross-sectional comparisons, two- or three-group comparisons will be performed using a t-test or ANOVA; if assumptions are not met, alternative nonparametric tests will be conducted (Mann–Whitney or Kruskal–Wallis test). Results will be considered statistically significant when *p* < 0.05. Correlations between selected parameters will be tested using Pearson or Spearman correlation, with prior tests for heteroscedasticity. Logistic and linear regression will be used to estimate associations between parameters. Missing data will be summarised by group with reasons; sensitivity analyses will assess robustness to missingness. Baseline total energy intake and baseline habitual dietary fibre intake from foods (excluding the allocated supplement) will be considered in prespecified sensitivity analyses (and in microbiome association models where relevant) to account for background diet; total fibre intake including the study supplement will not be included as a covariate in the primary efficacy model. For high-dimensional outcomes (e.g., microbiome taxa, metabolomics/VOCs), false discovery rate (Benjamini–Hochberg) control will be applied.

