The protocol and the aims of our RCT were developed by an interdisciplinary research team. Well-trained researchers will follow all rigorous procedures established for this RCT to ensure that the research is conducted according to standards of best practice. Another strength of this RCT is that it is a prospective study with a comparable healthy subject control group. We expect that the wide spectrum of results obtained will provide new insights into the impact of ITFs on the range of physiological, functional, and health-related parameters, from changes in gut microbiota characteristics and intestinal barrier function to health-related and metabolic biomarkers of the gut-skin axis. This research may elucidate the nature of the interaction between gut microbiota and skin, providing further insights into the functioning of the gut-skin axis. Given the important physiological role of gut microbiota, our study will be a pioneer in assessing the efficacy of ITFs in restoring gut homeostasis in individuals with PS and will also determine whether ITF-induced microbiota modulation is an effective method for alleviating inflammation and reducing the severity of PS-related skin lesions. We anticipate that the findings from our study will enable the development of personalised dietary therapies involving ITFs, which would avoid the side effects associated with other conventional psoriasis treatments. It is worth emphasising that the proposed prebiotic intervention approach is safe, relatively straightforward to implement, and could enhance current management strategies for this dermatosis. Ultimately, we aim for our research to support a nutritional therapeutic approach for regulating systemic immunity by manipulating the gut microbiota. Specifically, we seek to stimulate the growth and activity of beneficial pro-health bacteria. We believe that such dietary modifications may help reduce the metabolic disorders commonly associated with the development of psoriasis.

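### The plan promises a causal answer on the microbiota but states only association methods, and none of them names treatment arm

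*Protocol article*

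**What the plan says.** The Study objective section expects the trial to "determine whether the identified health-related benefits are evoked by compositional and/or functional changes of the intestinal bacterial communities". The section on strengths, risks and limitations repeats the aim: the trial will "determine whether ITF-induced microbiota modulation is an effective method for alleviating inflammation and reducing the severity of PS-related skin lesions". The discussion paragraph of the Abstract and the closing paragraph of the strengths and limitations section make the same kind of claim. The Hypothesis section sets out the presumed chain from microbiome through gut barrier and systemic inflammation to skin.

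The Statistical analysis plan section gives three tools that could bear on this aim:

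- Two-variable correlation: "Correlations between selected parameters will be tested using Pearson or Spearman correlation, with prior tests for heteroscedasticity".
- Regression, with no covariates listed for this purpose: "Logistic and linear regression will be used to estimate associations between parameters".
- Microbiome association models, mentioned where baseline energy and habitual fibre intake are to be considered "and in microbiome association models where relevant) to account for background diet".

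Treatment group is named as a predictor for the primary PASI model, and the PASI50 model takes the same adjustment set. It is not named for any of the three tools above. The section does not say whether correlations are pooled over arms, run within arm, or computed on values or on changes. The general threshold is "Results will be considered statistically significant when *p* < 0.05". For high-dimensional outcomes such as taxa and volatile compounds, "false discovery rate (Benjamini–Hochberg) control will be applied".

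**The concern.** To say that a benefit is evoked by a microbiota change is a statement about mediation: arm acts on microbiota, and microbiota acts on skin or inflammation. Randomisation supports the effect of arm on each of these. It does not support the step from microbiota to outcome, because the microbiota is not itself randomised.

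A Pearson or Spearman correlation is a two-variable statistic and carries no adjustment. Suppose the supplement raises a taxon and also, by some other route, lowers PASI. Prebiotic patients will then tend to have more of the taxon and lower PASI than placebo patients, and the pooled sample will show a correlation even if, within each arm, no patient's PASI follows that patient's microbiota. The better the supplement works on both variables, the more easily this would be read as evidence of mechanism. What is at stake is the trial's main mechanistic conclusion; the PASI efficacy result is not touched.

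**Working it through.** **Inputs from the Sample size section.** 25 evaluable per arm, standardised PASI difference 0.8, two-sided 5%, 80% power.

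**The plan's own figure.** By the normal approximation, n per arm = 2(1.960 + 0.842)² / 0.8² = 24.5, so 25. The stated number reproduces. (The t-based value is 25.5, and t-based power at 25 per arm is 79.1%.)

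**Assumed input.** The article gives no supplement effect on any taxon. I call it d_M and take 0.3 to 1.5 SD, with zero as the reference case. The effect on PASI change is d_Y = 0.8 SD as planned, with 0.5 SD and zero as alternatives.

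**Correlation created by arm alone.** With equal arms, unit within-arm variances and no within-arm link,

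ρ = (d_M·d_Y/4) / √[(1 + d_M²/4)(1 + d_Y²/4)] in absolute size.

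- d_M = 0.3, d_Y = 0.8: 0.06 / √(1.0225 × 1.16) = 0.055
- d_M = 0.8, d_Y = 0.8: 0.16 / 1.16 = 0.138
- d_M = 1.5, d_Y = 0.8: 0.30 / √(1.5625 × 1.16) = 0.223

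**Chance that one pooled test is significant.** Simulation, 20,000 trials per setting, 25 + 25 patients, d_Y = 0.8:

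| d_M (assumed) | Pooled Pearson | Pooled Spearman | Adjusted for arm |
|---|---|---|---|
| 0 | 5.0% | 5.3% | 5.0% |
| 0.3 | 6.6% | 6.6% | 4.8% |
| 0.5 | 9.5% | 9.5% | 4.8% |
| 0.8 | 15.8% | 16.0% | 5.0% |
| 1.0 | 21.4% | 21.8% | 5.0% |
| 1.2 | 27.2% | 27.6% | 4.9% |
| 1.5 | 35.5% | 36.4% | 5.1% |

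**Hand check by Fisher's z.** At 0.8/0.8, atanh(0.138) × √47 = 0.95, and P(Z > 1.96 − 0.95) plus the small opposite tail is about 16%. At 1.5/0.8, atanh(0.223) × √47 = 1.55, which gives about 34%. Both are close to the simulation.

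**Sensitivity.** With d_Y = 0.5 the Pearson rate is 7.2% at d_M = 0.5 and 17.7% at d_M = 1.5. With d_Y = 0 it stays at about 5% for every d_M. If all 30 randomised patients per arm were evaluable, with d_Y = 0.8, it is 11.0% at d_M = 0.5 and 41.9% at d_M = 1.5, so more patients make the problem larger.

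**Does the planned multiplicity control help?** No. The pooled correlation is truly non-zero (0.055 to 0.223 above). Benjamini–Hochberg limits findings that arise by chance; it does not turn a correlation produced by arm into a null one.

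**The case against.** The strongest reply is that the article is silent, not wrong. It nowhere says that correlations will be pooled and unadjusted, and covariates for exploratory association work are commonly left to a fuller analysis plan. This stands in part. A reader might infer that the plan commits to unadjusted pooled correlations; the text does not say so, and the inflation is conditional on that choice. A reader might also infer that the mechanistic claim rests on correlations alone. The regressions and microbiome association models are planned too, and they could include arm.

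The figures also have limits. They are per-test rates at an unadjusted 5%, they depend on an assumed taxon effect, and they need a real PASI effect. They are not the rate at which this trial would declare a false mechanism. Nor do they show what would happen if T0 and T1 values or healthy subjects were pooled: the article does not state such pooling, and the calculation above does not cover it.

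Finally, the objective is introduced as an expectation, the primary endpoint is PASI change analysed by arm, and the trial is presented as proof of concept. That limits the impact.

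The mismatch itself remains. The causal wording is in the article, in several places, and an unseen analysis plan does not change that wording. The article's own analysis section is specific about covariates elsewhere: it names diet variables for the microbiome models but not arm, the one variable expected to shift both sides.

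**Conclusion.** The concern holds as a mismatch between a causal aim and methods that can show only association, together with a conditional bias. If correlations are pooled over the arms without adjustment, which the text does not exclude, one test at 5% is significant in about 7% to 36% of trials with no within-arm link. This rests on 25 per arm, a true PASI effect of 0.8 SD and an assumed taxon effect of 0.3 to 1.5 SD. With a PASI effect of 0.5 SD it is about 7% to 18% for taxon effects of 0.5 to 1.5 SD. If either effect is zero it is 5%.

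A reader might infer that adjusting for arm would then justify the causal wording. It would not. Adjustment restores the error rate, but the microbiota is not randomised, and its change is measured over the same T0 to T1 interval as the change in PASI, so the order of events is not established. The point should be corrected; it does not affect the validity of the primary analysis.

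**What to change.** 1. In the Statistical analysis plan section, state that the mechanism analyses use T0-to-T1 changes in randomised patients only, as partial correlations or regressions adjusted for arm and for the baseline values of both variables. Keep the Benjamini–Hochberg control.
2. Label these analyses exploratory, and any mediation model likewise, and give the two reasons: the microbiota is not randomised, and it is measured over the same interval as PASI. A mediation model with one or two mediators named in advance is optional.
3. Reword the aim in the Abstract's discussion paragraph, the Study objective section, and both places in the strengths and limitations section, along the lines of: *explore whether benefits are associated with microbiota changes*.

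The cost is a few sentences and a more modest mechanistic claim. No new patients, samples or visits are needed, and the primary PASI analysis stays as it is.

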### Hypothesis

We hypothesised that supplementation of PS subjects with prebiotic ITFs would restore gut microbiome homeostasis, improve gut barrier function, and reduce systemic inflammation, which would consequently lead to alleviation of inflammatory symptoms and a decrease in the severity of skin lesions.

## Methods

### Study design

A single-centre, randomised, placebo-controlled, double-blind clinical trial with parallel arms and equal allocation is proposed. Additionally, a control group of healthy subjects will be established. The study adheres to the Consolidated Standards of Reporting Trials (CONSORT) 2010 [23] and Standard Protocol Items: Recommendations for Interventional Trials (SPIRIT) 2013 Statements [24] (Related file). The trial has been registered at ClinicalTrials.gov (NCT05971992) on August 1, 2023.

### Participants

The participants will be recruited by a dermatologist among the adult patients diagnosed with PS, who are inpatients and outpatients of the Clinic and Department of Dermatology, Sexually Transmitted Diseases and Clinical Immunology of the Municipal Hospital in Olsztyn (Poland). The PS patients will be invited by phone to participate in the study voluntarily (Fig. 1). Eligible patients interested in the study will be scheduled for an enrolment visit to the Dermatology Clinic. Mild PS patients (PASI < 10) [2] who will voluntarily give their informed consent form and meet the inclusion and exclusion criteria (Table 1) will be enrolled in the study group.

**Fig. 1 Fig1:**
[figure not shown]
Flow diagram of participant recruitment according to CONSORT [23]

Healthy individuals will be invited to participate in the study voluntarily through an advertisement posted on the Institute of Animal Reproduction and Food Science of the Polish Academy of Sciences (IAR&FR PAS) website (www.pan.olsztyn.pl). Individuals interested in the study will be scheduled for the enrolment visit at the Dermatology Clinic to sign the informed consent form. They will undergo the eligibility assessment (Table 1). Ultimately, healthy subjects who meet the inclusion and exclusion criteria will be enrolled in the control group (Fig. 1).

**Table 1 Tab1:** Criteria for inclusion and exclusion

Study group	Control group
Inclusion Criteria	Inclusion Criteria
• Age 18–65 years old • Mild psoriasis (PASI < 10) • Body mass index (BMI) < 30 kg/m^2^ • Omnivorous diet, • Negative tTG-IgA, • Willingness to give informed consent	• Age 18–65 years old • Good health • Body mass index (BMI) < 30 kg/m^2^ • Omnivorous diet, • Negative tTG-IgA, • Willingness to give informed consent
Exclusion Criteria	Exclusion Criteria
• Chronic or acute inflammatory disease (other than psoriasis), in particular diabetes, gastrointestinal disease, cardiovascular complications, heart, kidney and liver failure, thyroid disease, cancer • Current anti-psoriatic treatment (systemic or biologic) • Antibiotics within 14 days before sampling • Probiotic, prebiotic, and/or synbiotic supplements intake within 4 weeks before sampling • Pregnancy, breastfeeding • Surgery within 6 months before sampling	• Chronic or acute diseases, in particular, skin disease, diabetes, gastrointestinal disease, cardiovascular complications, heart, kidney and liver failure, thyroid disease, cancer • Antibiotics within 14 days before sampling. • Probiotic, prebiotic, and/or synbiotic supplements intake within 4 weeks before sampling • Pregnancy, breastfeeding • Surgery within 6 months before sampling

### Supplements

In this single-centre, double-blind, randomised placebo-controlled trial with 8-week nutritional intervention, a prebiotic ITFs formulation (Orafti^®^Synergy1, Beneo, Tienen, Belgium), consisting of a unique combination of chicory-derived inulin fractions with selected chain lengths (shorter chain (DP 3–9) and longer chain (DP ≥ 10) inulin in essentially equal amounts), was applied. According to the International Scientific Association for Probiotics and Prebiotics (ISAPP) statement, fructans are scientifically proven prebiotics of the most extensively documented health benefits in humans [25]. Additionally, the US Food and Drug Administration has announced that chicory root fibre is an approved dietary fibre [26]. Maltodextrin (Nutridex, OMNİA EUROPE SA., Medgidia, Romania), an odourless powder with an appearance and taste similar to ITFs, was selected as the placebo supplement in this RCT. This polysaccharide, easily digested and largely absorbed in the small intestine, is a common choice in ITFs studies [27, 28]. Thus, in our RCT, we chose maltodextrin based on guidance from the literature and our previous experience [29]. Both supplements were portioned into identical-looking, moisture-impermeable sachets by the outsourcing company (EDPOL Food & Innovation Sp. z o.o., Łomża, Poland). Each sachet contained 7.5 g of the appropriate powder. Packages containing the required number of sachets, either prebiotic or placebo, were prepared for the entire intervention period to be distributed to the enrolled participants.

